### **6.2 Secondary outcomes**

#### **6.2.1 Incidence of *C. difficile* diarrhoea (CDAD)**

Incidence of *C. difficile* diarrhoea, as diagnosed by a positive *C. difficile* toxin test and stool culture on all patients with undiagnosed diarrhoea. These tests to be conducted by the hospital laboratories.

Bowel function will also be monitored throughout (i.e. stool type; duration of diarrhoea; occurrence of diarrhoea / constipation)

#### **6.2.2 Duration of diarrhoea**

In the current study the duration of diarrhoea, defined as two or more loose stools, Bristol Stool Scale type 5 or above, will be collected in addition to the sole occurrence of diarrhoea.

#### **6.2.3 Change in prevalence of *C. difficile* toxin genes**

YHER will use TaqMan PCR as a more sensitive test for toxigenic *Clostridium difficile*. This may be done for a subset of samples or all samples, depending on resources available.

#### **6.2.4 Change in gut microbiota (stool specimen analysis)**

Further analysis of major bacterial groups in faecal samples may also be performed by YHER.

#### **6.2.5 Quality of life**

Patients' quality of life (WHO-QoL: Spinal Cord 48:762-769; Spinal Cord 50:112-118).

### **6.3 Outcome assessors**

Assessments will be carried out by trained, dedicated Research Assistants under supervision of the PI.

## **7 Statistical planning**

### **7.1 Hypothesis**

It is hypothesised that maintenance of a healthy commensal microbiota during antibiotic treatment by administration of a daily probiotic (*Lactobacillus casei* Shirota, as Yakult) will significantly reduce the occurrence of AAD and CDAD, and thus improve quality of life in spinal cord injury patients over time in comparison to the placebo control

The study success is defined as follows: a 17.9% lower occurrence of diarrhoea in the intervention group when compared to the control group.

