### **5.5.3 Randomisation: blinded treatment. Group allocation**

Following enrolment, participants will be randomised to either the intervention or placebo group. Random assignment will be performed by [name]. To ensure balanced groups for interim safety analysis, we will utilise a block randomisation technique, with permuted blocks of 30 for each study centre and for previous antibiotic use (15 to group 1 and 15 to group 2 per block), until sample size criteria are met.

Participants, medical and nursing staff, and investigators (study field staff) will also be blinded to allocation for the probiotic or placebo. The study code will be kept by the study statistician who will have no clinical role and no contact with patients.

After the study's opening assessment is completed (section 5.5.2), the randomisation list will be forwarded to the product distributor (Yakult Europe BV) by the Trial Statistician. Yakult Europe B.V. will arrange for product packs to be delivered, each with a sticker / code specific for each participant. This will ensure the hospital researchers are blinded to verum or placebo.

The placebo will be in identical packaging and of similar appearance and taste. The placebo has been used in several European studies and proven to be effective for blinding purposes.

Study field staff will be unaware to which group the subjects are assigned. See Appendix 5 for the decision tree outlining recruitment and randomisation of subjects. The study code will be kept by the study statistician who will have no clinical role and no contact with patients. Communications via electronic means will be encrypted (AES256), as per Instauration's Standard Operating Procedure.

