## **7.2 Sample size considerations**

Based on pilot data, this study aimed to find a difference of 17.9% in the proportion of patients with diarrhoea in two groups, (i) those on proton pump inhibitors – 56.3% and (ii) those on LcS – 38.4%. With  $\alpha=0.05$  and power of 90%, we estimate a sample size of 162 per group. After accounting for dropouts at 10% (across the length of the trial) this will require 180 per arm (total  $n=360$ ).

This sample size calculation is based on data from a single study site, but it seems reasonable to extrapolate the findings to other UK SCI centres. Therefore we aim to recruit 360 (180 per arm) in the proposed trial.

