## **7.4 Statistical analysis**

We will analyse the data using intention-to-treat principle. Fisher's exact test and  $\chi^2$  test will be used to compare rates of diarrhoea, as well as rates of AAD and CDAD. Relative risk and the number needed to treat, both with 95% confidence intervals, will be used to describe the treatment effect of probiotic. Logistic regression will be used to establish which factors influence the occurrence of diarrhoea. Continuous outcome measures will be analysed utilising ANCOVA (controlling for baseline scores and existing group differences) and multiple regression analyses ( $p<0.05$  critical value; sample size covers this analysis to a sufficient power level).

To reduce the bias implicit in utilising only complete cases, multiple imputation procedures for the laboratory data will be used using the SPSS (SPSS version 15, Inc, Chicago, IL) Markov Chain Monte Carlo multiple imputation function to produce 10 imputed datasets. These will then be analysed as normal; thereafter standard multiple

imputation procedures were used to combine the multiple scalar and multivariate estimates quantities.

To minimise confounding factors with respect to incidence of AAD and CDAD, stratification will be performed at the time of recruitment according to the antibiotic background (i) patients who have not previously received antibiotics in the 30 days prior to administration of intervention ('antibiotic-naïve') and (ii) patients who had been given a single antibiotic treatment for prophylactic purpose >14 days before first administration of intervention ('prophylactic-antibiotic').

In addition, a sub-group analysis will be performed on both treatment arms to analyse the following for association with AAD/CDAD occurrence: (i) risk of undernutrition, (ii) use of proton pump inhibitor, (iii) age  $\geq 65$  years and (iv) those receiving study drink within 24 hrs vs 48 hrs of first dose of antibiotics.

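### Section 7.1 makes the planning difference of 17.9 points the bar for success, so a trial with 90% power has only about a 50% chance of succeeding when the planned effect is exactly true

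*Protocol*

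**What the plan says.** Section 7.1 (Hypothesis) first gives the research hypothesis, which speaks of a significant reduction in AAD and CDAD. A separate sentence then sets the criterion: "The study success is defined as follows: a 17.9% lower occurrence of diarrhoea in the intervention group when compared to the control group". No test, significance level or confidence limit is attached, and the sentence does not say whether the percentage is absolute or relative.

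Section 7.2 (Sample size considerations) uses the same number as the design assumption: "this study aimed to find a difference of 17.9% in the proportion of patients with diarrhoea in two groups". The two rates are given as "those on proton pump inhibitors – 56.3" per cent and "those on LcS – 38.4" per cent. With alpha 0.05 "and power of 90%, we estimate a sample size of 162 per group", then raised to 180 per arm for 10% dropout. The synopsis repeats this calculation.

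Section 7.4 (Statistical analysis) plans Fisher's exact and chi-squared tests, with relative risk and number needed to treat and their 95% confidence intervals. Nothing in the protocol links the success criterion in 7.1 to these tests or to the stated power.

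**The concern.** A planning difference is a guess at the true effect, used to choose a sample size. A success criterion is a rule applied to the result. Section 7.1 uses one number for both. The estimated difference is centred on the true difference, so a bar set at the assumed truth is missed about half the time, whatever the sample size. The 90% in section 7.2 belongs to another rule, rejection of no difference at alpha 0.05, for which the bar is much lower.

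The protocol therefore holds two decision rules that can disagree. A clear, statistically significant reduction in AAD could fall short of success as defined. Alternatively, the choice between the two rules could be made once the results are known.

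**Working it through.** **Inputs.** Rates of 56.3% (p1, taken here as the control rate) and 38.4% (p2), alpha 0.05, power 90%, 162 evaluable and 180 recruited per arm (section 7.2). Allocation is 1:1 (section 5.5.3). The tests are chi-squared and Fisher's exact (section 7.4). Two-sided testing is my assumption: the protocol does not state it, but it reproduces the stated size, whereas one-sided testing gives 132.

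**1. The protocol's own figure.** Usual two-proportion formula with pooled variance under the null and no continuity correction:

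n = [1.96·√(2·p̄·(1−p̄)) + 1.2816·√(p1(1−p1) + p2(1−p2))]² / (p1−p2)², with p̄ = (0.563 + 0.384)/2 = 0.4735

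- √(2 × 0.4735 × 0.5265) = 0.7061
- √(0.2460 + 0.2365) = 0.6947
- n = (1.3840 + 0.8903)² / 0.179² = 161.4, rounded up to 162
- 162/0.9 = 180

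Power at 162 per arm is 90.1% by this approximation. The stated 162, 180 and 90% all reproduce, so the sizing arithmetic is not in question.

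**2. Bar for significance at 162 per arm.**

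1.96 × √(2 × 0.4735 × 0.5265/162) = 1.96 × 0.0555 = 0.109, or about 10.9 points.

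A difference of 14 points gives z = 0.14/0.0555 = 2.52, p about 0.012. It is significant but below 17.9 points.

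**3. Chance of meeting section 7.1 when the planned rates are exactly true.**

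SE = √[(0.563 × 0.437 + 0.384 × 0.616)/162] = 0.0546

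P(difference ≥ 0.179) = 1 − Φ((0.179 − 0.179)/0.0546) = 1 − Φ(0) = 50%

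Exact enumeration of the two binomial distributions gives:

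| | 162 per arm | 180 per arm |
|---|---|---|
| P(difference ≥ 17.9 points) | 52.4% | 48.9% |
| P(significant for LcS, chi-squared, two-sided 0.05) | 90.3% | 92.9% |
| P(significant for LcS, Fisher's exact) | 88.2% | 91.3% |
| P(significant by chi-squared but below 17.9 points) | 37.9% | 44.0% |

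The last row is the second minus the first: in this enumeration a difference of 17.9 points or more is always significant as well. Requiring both conditions therefore leaves the chance at 52.4% and 48.9%.

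The exact values straddle 50% because counts are whole numbers. With 162 per arm, 0.179 × 162 = 29.0, so 29 fewer cases suffice (29/162 = 0.1790). With 180 per arm, 0.179 × 180 = 32.2, so 33 fewer are needed.

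**4. True effect needed for a 90% chance under section 7.1.**

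0.179 + 1.2816 × 0.0546 = 0.249, or about 25 points, holding the SE at its planned value.

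**5. Other readings of the sentence.**

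- Relative reduction: 0.179 × 56.3 = 10.1 points. An observed relative reduction of at least 17.9% would occur in about 94% of trials at 162 per arm.
- Confidence limit beyond 17.9 points: if the true difference is 17.9, the lower limit of a 95% interval exceeds it in about 2.5% of trials.

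Neither reading gives the 90% of section 7.2.

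**The case against.** The best defence is that the sentence is loose wording for the target effect. It stands under the heading Hypothesis, directly after a statement that speaks of a significant reduction, and it never says that the difference is the observed one. Section 7.4 fixes the tests and the effect measures, and no stopping, reporting or publication rule depends on 17.9%. A significant 14-point reduction would still be tested and reported with its interval. On this view the 90% is correct for what it describes, and only a label is at stake.

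Part of this stands. The word observed is an interpretation, the 90% is right as the power of the significance test, and neither estimates nor data are affected. But the sentence is introduced as the definition of success, and section 7.2 already states the target effect. Treating a size of difference as a threshold on the result is the plain reading, and the alternatives in step 5 do not restore agreement with section 7.2. Adding significance from the preceding paragraph leaves the chance at about 50%. Nor is this a detail left for a SAP: the protocol itself fixes a rule, and the rule conflicts with its own power statement.

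The absolute-or-relative ambiguity is secondary, since section 7.2 obtains 17.9 as a difference of two proportions. Section 7.2 also attaches the 56.3% to patients on proton pump inhibitors instead of placebo. That is a separate problem and hardly alters the result here: a bar equal to the assumed effect is met about half the time at any baseline rate.

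**Conclusion.** The concern holds. As written, the success rule in section 7.1 conflicts with the test for which section 7.2 powers the trial. If the planned effect is exactly true, the chance of success is about 50% (exact 52.4% at 162 per arm, 48.9% at 180), against about 90% for a significant result. About 38% of trials at 162 per arm would be significant without meeting the definition. A larger sample does not cure this; only a true effect of about 25 points would give a 90% chance.

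This rests on reading 17.9% as an absolute difference that the result must reach, on two-sided alpha 0.05, and on 56.3% and 38.4% as the true control and LcS rates. It must be corrected, because it is the protocol's only definition of success.

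**What to change.** Replace the success sentence in section 7.1 with wording such as:

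> Success is a statistically significant (two-sided p<0.05) lower proportion of patients with AAD on LcS than on placebo in the primary analysis, reported as absolute risk difference and relative risk with 95% confidence intervals. The 17.9 percentage points (absolute) in section 7.2 are the planning difference only.

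The primary analysis should be tied to one of the two tests named in section 7.4, since they can disagree near the threshold (power at 162 per arm is 90.3% for chi-squared and 88.2% for Fisher's exact). The label on the 56.3% in section 7.2 should be settled at the same time, so that the planning difference refers to LcS against placebo.

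The cost is a sentence or two in a protocol amendment. Sample size, randomisation, data collection and patients are unaffected. The change should be made before unblinding.

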## **7.2 Sample size considerations**

Based on pilot data, this study aimed to find a difference of 17.9% in the proportion of patients with diarrhoea in two groups, (i) those on proton pump inhibitors – 56.3% and (ii) those on LcS – 38.4%. With  $\alpha=0.05$  and power of 90%, we estimate a sample size of 162 per group. After accounting for dropouts at 10% (across the length of the trial) this will require 180 per arm (total  $n=360$ ).

This sample size calculation is based on data from a single study site, but it seems reasonable to extrapolate the findings to other UK SCI centres. Therefore we aim to recruit 360 (180 per arm) in the proposed trial.

## **7.3 Sample per Investigative Site**

Estimated annual recruitment rates for the following participating centres are:

- National Spinal Injuries Centre, Stoke Mandeville Hospital: 9/month; 108 /year.
- The Midlands Centre for Spinal Injury, The RJ&AHO Hospital: 4/month; 48 /year.
- The Princess Royal Spinal Injuries Centre, Northern General Hospital: 3/month; 36/year.

## **7.4 Statistical analysis**

We will analyse the data using intention-to-treat principle. Fisher's exact test and  $\chi^2$  test will be used to compare rates of diarrhoea, as well as rates of AAD and CDAD. Relative risk and the number needed to treat, both with 95% confidence intervals, will be used to describe the treatment effect of probiotic. Logistic regression will be used to establish which factors influence the occurrence of diarrhoea. Continuous outcome measures will be analysed utilising ANCOVA (controlling for baseline scores and existing group differences) and multiple regression analyses ( $p<0.05$  critical value; sample size covers this analysis to a sufficient power level).

To reduce the bias implicit in utilising only complete cases, multiple imputation procedures for the laboratory data will be used using the SPSS (SPSS version 15, Inc, Chicago, IL) Markov Chain Monte Carlo multiple imputation function to produce 10 imputed datasets. These will then be analysed as normal; thereafter standard multiple

imputation procedures were used to combine the multiple scalar and multivariate estimates quantities.

To minimise confounding factors with respect to incidence of AAD and CDAD, stratification will be performed at the time of recruitment according to the antibiotic background (i) patients who have not previously received antibiotics in the 30 days prior to administration of intervention ('antibiotic-naïve') and (ii) patients who had been given a single antibiotic treatment for prophylactic purpose >14 days before first administration of intervention ('prophylactic-antibiotic').

In addition, a sub-group analysis will be performed on both treatment arms to analyse the following for association with AAD/CDAD occurrence: (i) risk of undernutrition, (ii) use of proton pump inhibitor, (iii) age  $\geq 65$  years and (iv) those receiving study drink within 24 hrs vs 48 hrs of first dose of antibiotics.

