### 4.2 Secondary Objectives

To analyse the effect of LcS on the

- Occurrence of *C. difficile* diarrhoea (CDAD)
- Duration of diarrhoea
- Change in gastrointestinal microbiota (stool specimen analysis)
- Quality of life

- To determine if malnutrition (undernutrition) is a risk factor for AAD and CDAD
- To determine if use of proton pump inhibitors (PPI) is a risk factor for AAD and CDAD.

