#### 5.5.2 Study procedure: opening assessments

After having obtained informed consent (1x copy to patients; 1x copy in medical notes; 1 x original in the investigator site file), basic patient's clinical characteristics and baseline measurements, as outlined on the Case Report Form (CRF, see [Item 12.1](#)), will be collected. No intervention will be administered prior to the completion of the study opening visit.

- Baseline demographics and clinical data
- Record use of medications (including use of antibiotics, laxatives, anti-diarrhoeal agents, proton pump inhibitors, H2 blocker)
- Nutrition risk scores – Spinal Nutrition Screening Tool (Wong et al, 2010, 2012)

- Quality of Life evaluation – WHO-QoL BREF ([http://www.who.int/substance\\_abuse/research\\_tools/en/english\\_whoqol.pdf](http://www.who.int/substance_abuse/research_tools/en/english_whoqol.pdf))
- Bowels function measures – stool type, duration of diarrhoea  
Definition of diarrhoea: two or more loose stools, Bristol Stool Scale (O'Donnell LD, 1990) type 5 or above.  
Constipation: using Rome III criteria: Functional constipation ([http://www.romecriteria.org/assets/pdf/19\\_RomeIII\\_apA\\_885-898.pdf](http://www.romecriteria.org/assets/pdf/19_RomeIII_apA_885-898.pdf)) (Drossman DA, 2006).
- Stool Specimen analysis (Kubota *et al.* 2014)  
One sample will be taken, frozen and stored frozen and then sent to YHER for TaqMan PCR analysis of toxigenic *C. difficile*. This analysis will be dependent on available resources at YHER. Further microbial analysis may also be done. This will be in the participant information sheet and on the consent form.

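### The primary AAD comparison in 7.4 is unadjusted, although candidate risk factors are recorded at baseline; adjusting for them could add a modest amount of precision that the protocol does not allow to be sized.

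*Protocol*

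**What the plan says.** **Primary comparison.** In Protocol 7.4 Fisher's exact test and the chi-square "test will be used to compare rates of diarrhoea, as well as rates of AAD and CDAD". Relative risk and NNT, each with a 95% CI, describe the treatment effect. No covariate enters.

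**Logistic model.** The same section adds: "Logistic regression will be used to establish which factors influence the occurrence of diarrhoea". It lists no covariates and does not name treatment as a term.

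**Adjustment elsewhere.** 7.4 plans ANCOVA with baseline control for continuous outcomes only.

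**Candidate factors.** 4.2 sets as an objective: "To determine if use of proton pump inhibitors (PPI) is a risk factor for AAD and CDAD". It sets the same question for undernutrition. The sub-group paragraph of 7.4 lists undernutrition risk, PPI use and age 65 or over for association with AAD/CDAD.

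**Baseline data.** 5.5.2 collects demographics, medication use including PPIs, and "Nutrition risk scores – Spinal Nutrition Screening Tool" results before the first study drink.

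**Sample size.** 7.2 says "this study aimed to find a difference of 17.9% in the proportion of patients with diarrhoea in two groups", with "those on proton pump inhibitors – 56.3" per cent against "those on LcS – 38.4" per cent, and "power of 90%, we estimate a sample size of 162 per group".

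**The concern.** A baseline variable that predicts AAD carries information about the outcome that a two-by-two table does not use. If PPI use, nutrition risk or age predict AAD, leaving them out makes the confidence interval somewhat wider than the collected data require.

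None of the three is a randomisation factor: 5.5.3 blocks on centre and previous antibiotic use only. A chance imbalance in them can therefore shift the observed risk difference in the one trial that is run. The usual standard error allows for such imbalance on average, but the unadjusted estimate does not correct for the imbalance that actually occurs.

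The protocol accepts baseline adjustment for continuous outcomes and gives no reason for treating the primary binary outcome differently. The stake is precision, not validity.

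**Working it through.** **1. Reproduce the planned figure.** Inputs from 7.2: p0 = 0.563, p1 = 0.384, difference 0.179, alpha 0.05 taken as two-sided, power 90%. Pooled-variance formula without continuity correction, with mean rate (0.563 + 0.384)/2 = 0.4735:

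- 1.960 × √(2 × 0.4735 × 0.5265) = 1.960 × 0.7061 = 1.384
- 1.282 × √(0.563 × 0.437 + 0.384 × 0.616) = 1.282 × 0.6947 = 0.890
- n = (1.384 + 0.890)² / 0.179² = 5.172 / 0.03204 = 161.4, rounded up to **162 per group**
- 162 / 0.90 = **180 per arm**

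Both match. Power at 162 per group is 90.1%. The sample size therefore rests on the unadjusted comparison and agrees with it.

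**2. Gain if the covariates explain a share R² of the AAD variance.** The protocol gives no R², so these values are assumptions. Adjustment scales the variance by (1 − R²). The effective n is 162/(1 − R²), and the n needed for the same power is 162 × (1 − R²), rounded up.

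| Assumed R² | Effective n per group | Power at 162 | n per group for the same power |
|---|---|---|---|
| 0% | 162.0 | 90.1% | 162 |
| 1% | 163.6 | 90.4% | 161 |
| 2% | 165.3 | 90.7% | 159 |
| 5% | 170.5 | 91.5% | 154 |
| 10% | 180.0 | 92.9% | 146 |
| 15% | 190.6 | 94.1% | 138 |

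In terms of the estimate, the unadjusted standard error is √((0.2460 + 0.2365)/162) = 5.46 points, a 95% half-width of 10.7 points. At R² = 15% it is 5.46 × √0.85 = 5.03 points, a half-width of 9.9.

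**3. What R² might be.** For binary factors with risk difference d and prevalence q, R² ≈ Σ d²q(1 − q) / (0.4735 × 0.5265).

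- One factor, d = 17.9 points, q = 50% (both assumed): 0.0320 × 0.25 / 0.2493 = 3.2%.
- Adding factors of 15 points at 40% and 10 points at 30% (assumed): (0.0080 + 0.0054 + 0.0021) / 0.2493 = 6.2%.
- Effective n is then 167.4 and 172.7, and power 91.0% and 91.8%.

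**4. Simulation.** 324 patients, 3,000 trials per scenario, three binary covariates with assumed prevalences of 40%, 40% and 25%, and marginal rates held at 56.3% and 38.4%. The adjusted risk difference comes from the logistic model by standardisation.

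| Assumed covariate ORs | Variance ratio, adjusted/unadjusted | Power, chi-square | Power, adjusted logistic |
|---|---|---|---|
| 1, 1, 1 | 1.01 | 90.5% | 90.2% |
| 1.5, 1.5, 1.5 | 0.98 | 90.6% | 91.0% |
| 2, 2, 2 | 0.94 | 89.6% | 91.3% |
| 3, 2, 2 | 0.91 | 90.9% | 93.5% |
| 3, 3, 3 | 0.85 | 90.3% | 93.8% |
| 4, 3, 2 | 0.87 | 89.1% | 92.9% |

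The Monte Carlo error of each power is about √(0.9 × 0.1/3,000) = 0.5 points. Fisher's exact test had 87% to 89% in the same runs. Centre and prior antibiotic use were not simulated.

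**5. Chance imbalance.** With an assumed PPI prevalence of 50% and 162 per arm, the between-arm difference in prevalence has SD √(2 × 0.25/162) = 5.6 points, so about ±11 points is ordinary. With an assumed 17.9-point PPI effect this moves the risk difference by 0.11 × 17.9 ≈ 2 points.

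**6. Can the model be supported?** Expected AAD cases are 0.4735 × 324 ≈ 153. With linear terms for age and nutrition score, the model has seven terms besides the intercept: treatment, PPI, nutrition risk, age, two for three centres, and one for prior antibiotics. That is about 22 cases per term.

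**The case against.** The case against is substantial. An unadjusted comparison of randomised arms is valid, the sample size was built for it, and the chi-square test delivers the planned power. The gain rests wholly on assumed prognostic strength and may be nil. All of that stands, and it keeps this a minor point.

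Four stronger readings are tempting, and the protocol does not support them:

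- *The trial ignores known risk factors.* 4.2 asks whether PPI use and undernutrition are risk factors. Age is not in 4.2 and appears in 7.4 only as a sub-group. They are candidates.
- *The planned logistic model already supplies the adjusted effect.* It is a factor-finding model without a stated treatment term, covariate list or standardisation. The fix needs a new treatment-effect model.
- *The analyses compete without priority.* 7.4 gives the tests, relative risk and NNT the treatment-effect role and the logistic model a different one.
- *The 17.9 points measure the PPI effect.* 7.2 sets PPI users against LcS recipients, not against patients without PPIs, so the figure gives no usable prognostic strength. Its use above is an assumption only.

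It may also be said that covariates belong in an analysis plan that is not shown. But the protocol itself fixes the unadjusted tests as the comparison, so this is a choice made and not a detail left open.

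**Conclusion.** The point holds as a modest, optional improvement. The primary comparison may give up some precision and leaves the estimate uncorrected for chance imbalance in three recorded baseline variables. It is neither biased nor underpowered on that account.

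The size is about 0% to 15% lower variance, or about 0 to 4 points of power, for assumed covariate odds ratios from 1 (no effect) to 4. Moderate odds ratios of 1.5 to 2 give a 2% to 6% cut in variance. If the factors are not prognostic, adjustment gains nothing and costs about 1%. The range assumes binary covariates at the stated prevalences and complete baseline data. The protocol cannot narrow it.

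**What to change.** In 7.4, before unblinding, pre-specify the primary LcS effect on AAD as follows:

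- Fit a logistic model with treatment, opening-visit PPI use, opening-visit nutrition risk score and age, together with the randomisation factors (centre and prior antibiotic use). State the form of each term, for example whether age is continuous or split at 65.
- Standardise the fitted risks over all randomised patients to a marginal risk difference (NNT as its reciprocal) and relative risk, with 95% CIs by a named method. This keeps the planned effect measures and avoids switching to a conditional odds ratio.
- Use opening-visit values only, with a simple rule for missing ones. In Appendix 2 the PPI row shows no opening-visit mark although 5.5.2 records PPI use then. This may be table layout; confirm it against the CRF.
- Keep the unadjusted test as a supporting analysis.

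No new data are needed. The costs are a new model with a standardisation step, the missing-value rule, the roughly 1% loss if the covariates carry no information, and an ethics-reviewed amendment under section 12. Version 3.2 is dated May 2018 and completion is expected in Q3 2018, so time is short.
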